#### Effectiveness outcome - quality of care measures

i.)**Sample size**

We will randomly sample at least 50 charts per site. This will provide 95% confidence intervals with widths no greater than +/− 10% for percentages of patients meeting quality measures (QMs) within each site.
ii.)**Data collection and analysis**

Improvements in quality of care will be evaluated using QMs for each of the three CCAB order set domains [69] (see Table 3)**.** The majority of QMs will be obtained from administrative and chart review data audits from randomly selected charts and will take place quarterly during the study. The data from these audits will be used to promote change at each site. The central data collection team will record survey results in a secure AHS database for analysis. We will use inverse sampling weights to estimate the percent of patients attaining the QMs for the province. Administrative data will be analyzed for clinical outcomes, with additional analyses to compare change in QMs based on patient-reported outcomes, using linear mixed effects models that account for patient factors and observation clustering within sites [64].

**Table 3 Tab3:** Sample of Quality Measures (QMs)

Cirrhosis Care Alberta Order Set Domain	Quality Measure Definition

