In response to this “crisis in the making” [18], there has been much attention focused on strategies to reduce care gaps, improve quality of care and reduce readmissions in patients with cirrhosis [19–21]. For inpatients, these gaps can be summarized into three priority areas: i) management of cirrhosis complications, ii) management of broader health needs such as frailty, alcohol use disorder (AUD) and advance care planning and iii) preparation for transition of care into the community, including structured education and timely follow-up post discharge. There has been extensive data to support the presence of these care gaps in cirrhosis and emerging data to support the positive impact of solutions in each of these areas. For example, despite robust evidence that guideline-based care improves patient outcomes, including for those patients with cirrhosis, evidence-based guidelines are only utilized in 30–60% of patients [22–25]. An example of a successful solution in this area has been an electronic order set intervention implemented by Tapper et al. focused on inpatient management of hepatic encephalopathy and prophylaxis against spontaneous bacterial peritonitis. This intervention reduced 30-day readmission rates by 40% [26]. With regards to gaps in broader health needs, although greater than 50% of cirrhosis-related admissions can be attributed to alcohol [13], and it is clear that abstinence reduces hepatic decompensation, readmissions and mortality, in two recent series < 15% of patients received treatment for AUD [27, 28]. Similarly, malnutrition, sarcopenia and frailty are strong predictors for morbidity and mortality in patients with cirrhosis [29]. The management of malnutrition has been associated with lower hospital readmissions but structured care in this area is infrequent [30–32]. Lastly, there are gaps in in preparing patients for transition of care into the community. While it is clear that education improves patient knowledge, ability to self-manage their disease, and can even reduce the risk of re-hospitalization in populations such as heart failure, no hospital site in Alberta offers standardized discharge teaching to patients with cirrhosis [33, 34]. Moreover, the minority of patients have follow-up appointments arranged with primary and/or specialty care prior to discharge despite evidence that timely follow-up reduces mortality [35].

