### Study setting

Health care in the province of Alberta is publicly funded and includes access to medically necessary services for all residents. Alberta Health Services (AHS), is a single health authority responsible for decision-making and delivery of healthcare services at hundreds of sites in the province (hospitals, as well as various continuing care and community health programs). It is organized into five geographic zones (North, Edmonton, Central, Calgary and South) [57]. In late 2019, AHS introduced a province-wide Epic® based CIS known as Connect Care to consolidate 1300 clinical information systems in use across the province. The implementation of Connect Care will facilitate consistent practices and access to patient medical records across hospital care sites in the province, and will be implemented in nine waves across all five provincial health zones from November 2019 until the Fall of 2022.

Eight hospital sites in Alberta have been selected to participate in the study. Implementation of the CCAB order set intervention at the sites will be facilitated by the Connect Care rollout. The selection of hospital sites has been guided by a consideration of (i) urban vs. rural communities, (ii) type of hospital (academic vs. community), and (iii) prevalence of cirrhosis. The selection has also considered the importance of having representation from the five health zones comprising AHS. Table 1 shows the selected hospitals in each zone as well as the 2017 administrative data estimates of the prevalence of cirrhosis in each zone.

**Table 1 Tab1:** CCAB Project Hospital Sites

Zone	Age-Standardized Cirrhosis prevalence n(%)	Implementation sites
Edmonton Zone	3271(0.27)	4 (2 academic and 2 community hospitals)
Central Zone	1115 (0.24)	1 Community hospital
North Zone	986 (0.25)	1 Community hospital
Calgary Zone	3780 (0.26)	1 Academic hospital
South Zone	775 (0.27)	1 Community hospital

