### Sample size, data collection and analysis

#### Effectiveness outcomes - clinical outcomes, cost-utility

i.)**Sample size**

Consistent with the type 1 hybrid trial design, the overarching sample size calculation is based on the cumulative 90-day hospital length of stay (LOS) [48]. Based on 2015/2016 AHS administrative data (4176 cirrhosis-attributed admissions for 2652 patients at study sites) [62] and CCAB implementation time per site, we estimate a pre-intervention cohort of 3975 patients and post-intervention cohort of 3975 patients (n = 7950). Our calculations tested our ability to detect a 3-day reduction in average 90-day cumulative LOS from our historically observed average of 13.7 days. Computer simulations re-sampled historic LOS data to assess power to detect proposed effects for plausible scenarios using interrupted time series models with random intercepts for sites and an over-dispersed Poisson distribution. A scenario that assumed that 50% of eligible patients would receive the pathway (our most conservative estimate) and that there would be a rapid and sustained uptake of the pathway in the two years following implementation had > 90% power to detect an effect in the three largest sites and the whole cohort [63].
ii.)**Data collection and analysis**

The index population will be identified at admission with a validated Canadian algorithm of ICD9 and ICD10 codes (overall accuracy 87%) [58]. We will analyze administrative data (n = 7950) using linear effect modeling that accounts for patient factors and observation clustering within sites [64]. We will use segmented regression analyses of interrupted time series to model 90-day cumulative LOS and hospitalization rate in each period [65], comparing post-intervention changes with pre-intervention secular trends [66]. We will evaluate and account for autocorrelation or other serial dependencies in data. Each of five geographic zones and eight hospital sites will serve as its own control, enabling us to identify effectiveness within each jurisdiction. We will also combine site series into generalized linear mixed effects models [64], with a random intercept for each site, fixed effects for time, and an indicator variable for pre-and post-intervention periods for each site.

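### Fifty charts per site give a within-site 95% confidence interval of about ±14 points at worst, not the stated maximum of ±10

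*Protocol article*

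**What the plan says.** In the protocol article, the sample-size paragraph under *Effectiveness outcome - quality of care measures* reads: "We will randomly sample at least 50 charts per site". The next sentence says this will provide "95% confidence intervals with widths no greater than +/− 10% for percentages of patients meeting quality measures" within each site. It gives no expected percentage, interval method, finite-population correction or pooling of rounds.

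The data-collection paragraph of the same section says that the audits "will take place quarterly during the study", without saying whether the 50 charts are per quarter, per period or in total. It also says: "We will use inverse sampling weights to estimate the percent of patients attaining the QMs for the province".

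Table 3 lists 15 sample measures. Ten are conditional on a complication or a screening result: all nine under cirrhosis complications, and the alcohol use disorder measure.

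**The concern.** A maximum is a guarantee. It has to hold at the smallest planned sample (50) and at the least favourable percentage (50%). Fifty observations look too few for ±10 points at 95% confidence, and the middle of the scale, where the interval is widest, is where the measures may well lie: the Background says that "evidence-based guidelines are only utilized in 30–60% of patients".

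The conditional measures make the gap larger, because only charts of patients with the condition enter the denominator.

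Quality of care is a listed secondary effectiveness outcome, and the audit results are to be used to drive change at each site. A reader who trusts ±10 would think a site percentage better determined than it is.

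A smaller question is whether weights built from chart sampling can carry an estimate to the whole province, when the sites were chosen purposively.

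**Working it through.** **Inputs.** n = 50 charts per site and the 95% level come from the quality-of-care sample-size paragraph. The 30–60% range comes from the Background; it is cited guideline use, not a planning value, and serves only as a check. For a finite-population correction, the clinical-outcomes sample-size paragraph gives "4176 cirrhosis-attributed admissions for 2652 patients at study sites" for one year. Over eight sites the mean per site-year is 2652/8 = 331.5 patients or 4176/8 = 522 admissions.

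**The plan's own figure.** Half-width = 1.96 × √(p(1−p)/n). At p = 50%:
- n = 50: 1.96 × √(0.25/50) = 13.9 points.
- n = 97: 9.95 points. The requirement is n = 1.96² × 0.25/0.10² = 96.04, rounded up to 97.

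So ±10 corresponds to about 97 charts. At n = 50, ±10 corresponds to roughly 84% confidence.

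**Other 95% intervals, n = 50, p = 50%.** Wilson 13.4, Agresti-Coull 13.4, Jeffreys 13.5, Clopper-Pearson (exact) 14.5. None reaches 10.

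**Other percentages (Wald, n = 50).**

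| Percentage meeting the measure | Half-width (points) |
|---|---|
| 10% or 90% | 8.3 |
| 15% or 85% | 9.9 |
| 20% or 80% | 11.1 |
| 30% | 12.7 |
| 50% | 13.9 |
| 60% | 13.6 |

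The bound needs p(1−p) ≤ 50 × 0.01/1.96² = 0.130, so p ≤ 15.4% or p ≥ 84.6%.

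**Finite-population correction, p = 50%.** Multiply 13.86 by √((N−50)/(N−1)):
- N = 331.5: 12.8 points.
- N = 522: 13.2 points.

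Fifty charts reach ±10 only if the site population is about 103 or fewer. With the correction, ±10 needs 96.04/(1 + 95.04/N) charts: 75 for N = 331.5 and 82 for N = 522.

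**If 50 means per quarter (not stated).**
- Two pooled rounds, n = 100: 9.8 points.
- One round with a correction at a mean-sized site: 8.8 points on patients (N = 331.5/4 ≈ 83), 10.9 points on admissions (N = 522/4 ≈ 131). Larger sites would be wider.

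**Condition-specific measures.** The document gives no frequencies for the conditions, so these denominators are assumptions, all at p = 50%:
- half of charts qualify (n = 25): ±19.6 points;
- 30% qualify (n = 15): ±25.3 points;
- 20% qualify (n = 10): ±31.0 points, where the Wald formula is only a rough guide.

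**Weights.** *Study setting* says: "Eight hospital sites in Alberta have been selected to participate in the study". It describes selection by setting, hospital type, cirrhosis prevalence and zone representation, with no selection probabilities. The abstract's discussion treats the rest of Alberta as separate. Charts at other hospitals have no chance of being sampled, so inverse sampling weights alone scale up to the patients of the eight sites.

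**The case against.** The strongest defence is that 50 is a floor and the audits are quarterly. If 50 charts were meant per round and rounds are pooled, two rounds give ±9.8 and the claim comes true. That may be what the authors had in mind, but the sentence ties ±10 to 50 charts per site and mentions no pooling. It therefore needs correction or clarification either way.

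The 30–60% range is background, and the same section cites figures below 15% for treatment of alcohol use disorder, where 50 charts do give about ±10. That is true, but a maximum has to hold for every measure. Some measures also come from administrative data, so not every denominator is limited to 50 charts; this limits the reach of the point without rescuing the sentence.

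Two stronger readings are tempting. A reader might infer that 10-point changes at a site would be wrongly taken as real. The document sets no 10-point rule, and even if ±10 were right, a difference between two independent samples would carry about 10 × √2 = 14 points, so such a change would be unresolved anyway. A reader might also infer that a provincial estimate is impossible. The sites cover all five zones and Table 1 gives zone case counts, so a zone-weighted estimate under a stated model assumption is conceivable; the province may also be loose wording for the eight sites combined. What stands is that the chart-sampling weights alone do not reach the other hospitals.

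**Conclusion.** The stated precision is wrong as written. With 50 charts the worst-case within-site 95% half-width is about 14 points (13.4 to 14.5 depending on the interval method), roughly 40% wider than claimed (13.9/10). A finite-population correction at the mean site-year size brings it only to 12.8–13.2. That correction assumes mean-sized sites; the document gives no volume for each site, so a small one could do better and a large one would do worse. For the ten conditional measures in Table 3 the shortfall is larger by an amount the document does not allow one to fix.

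This is a should-fix point, not a threat to the trial. Quality of care is secondary, Table 2 assigns it to interrupted time series rather than to single-site intervals, and the sample size for 90-day cumulative length of stay does not depend on it. The point on the provincial estimate is a secondary matter of wording, resting on design reasoning rather than on a figure.

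**What to change.** 1. Replace the ±10 statement with: about ±14 percentage points (Wald interval, at 50%) for measures that apply to all 50 charts at a site. Naming the method matters, because the exact interval gives 14.5.
2. Add that condition-specific measures will be less precise, and report them pooled over sites or quarters.
3. If 50 was meant per quarter with rounds pooled, say so and give the resulting n; two rounds, n = 100, give ±9.8.
4. Describe the weighted percentage as applying to the eight study sites, unless the further assumption needed for the rest of the province is stated.

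The cost is wording, and a less favourable precision statement. Keeping ±10 from a single sample is optional and would take about 97 charts per site, or roughly 75 to 82 with a finite-population correction at a mean-sized site-year.

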#### Phase 3 – implementation

The final phase of the study will commence with “go-live” of the CCAB order set in the provincial CIS at each site. The order set will be implemented using a staged approach, timing determined by timing of CIS implementation across the province (months 12–33). Outcome effectiveness measures will be collected during this phase.

*ERIC Strategies within this phase: Audit and provide feedback. Capture and share local knowledge. Purposely re-examine the implementation. Tailor strategies.*

As sites enter phase 3, site champions will be invited to participate in monthly learning sessions (conducted virtually with representatives from each site) to discuss their experience, including barriers, facilitators, and lessons learned. Collection of Key Performance Indicators (KPIs) will occur quarterly and be shared with sites on electronic scorecards representing audit and feedback. The scorecards will include a combination of standard KPIs (e.g. order set utilization, length of stay) and site prioritized KPIs (e.g. performing a screen for alcohol use disorder). The rationale for including site prioritized KPIs is to promote site engagement and ownership of practice change. In the learning session following the quarterly release of scorecards, the teams will share learnings with each other and develop action plans to tailor implementation strategies at their sites. These Plan-Do-Study-Act (PDSA) cycles will continue quarterly throughout the implementation phase.

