### Evaluation

This hybrid trial evaluation is guided by the RE-AIM framework as summarized in Table 2. The outcome measures and data analyses plans are classified into effectiveness and implementation outcomes in accordance with the research questions.

**Table 2 Tab2:** Overview of the Cirrhosis Care Alberta (CCAB) evaluation methods

RE-AIM Domains	Outcomes	Measures	Data sources/ tools	Analytic Methods	Study Phase		
					1	2	3
Reach	Uptake	Proportion of care providers who participate in education interventions for the order set,	Program data, Administrative data,	Descriptive statistics		X	X
		Proportion of cirrhosis patients being managed using the CCAB order set	Chart reviews				
Effectiveness	Clinical and Cost-Utility	I.e.. Cumulative hospital LOS and readmission rates per patient year,	Administrative data,	Interrupted time series,	X		X
			Chart reviews	Incremental Cost-Effectiveness Ratio			
		Cost of care (health system perspective) QALYs gained					
	Patient reported outcome measures (PROMs)	Health-related quality of life,	Post-discharge phone surveys, EQ-5D and CTM questionnaires,	Descriptive and inferential statistics,	X		X
		Patient/family and provider experience					
				Framework and thematic analyses			
			Qualitative interviews				
	Quality Measures	Quality of care (eg. appropriate prescribing of rifaximin, screening for frailty, time to post discharge follow up)	Chart reviews	Interrupted time series	X		X
Adoption	Utilization	Number of hospital sites that use the orders sets/Number of hospital sites enrolled,	Administrative data,	Descriptive statistics,			X
			Qualitative interviews	Framework and thematic analyses guided by NPT and CFIR			
		Processes and determinants of adoption					
Implementation	Feasibility	Processes and determinants of feasibility and acceptability from patients, caregivers and health care providers’ perspectives	Qualitative interviews	Framework and thematic analyses guided by NPT and CFIR	X	X	X
	Fidelity	Proportion of order sets prescribed that adhere to the three core-components of the standardized CCAB order set	Administrative data	Descriptive statistics			X
Maintenance	Sustainability	Proportion of cirrhosis patients being managed using the CCAB order set 6 months after the research team has completed supported rollout	CCAB program implementation data,	Descriptive statistics,			X
				Framework and thematic analyses guided by NPT and CFIR			
			Qualitative interviews				

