**Preparation for transition into the community**	
Standardized cirrhosis education for patients/caregivers	Patients with cirrhosis should receive cirrhosis education prior to discharge
Post-discharge laboratory, diagnostic imaging and endoscopy appointments	Patients with cirrhosis should receive information about when to have lab work done post discharge
Post-discharge follow-up with primary and/or specialty care	*Recently discharged patients with cirrhosis should have a clinic visit with a health care provider within 4 weeks of discharge

Table includes a sample of the Quality Measures (QM) that will be evaluated from each domain of the Cirrhosis Care Alberta (CCAB) order set. Additional QMs will also be evaluated. QMs were selected based on consensus by either: *Practice Metrics Committee of the American Association for the Study of Liver Diseases [70], or consensus between the CCAB study team members

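### Quality measures taken from charts are compared across a change of recording system, so a change in recording can appear as a change in quality of care

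*Protocol article*

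**What the plan says.** The section Effectiveness outcome - quality of care measures gives the source: "The majority of QMs will be obtained from administrative and chart review data audits from randomly selected charts", with audits each quarter. The sample is set by "We will randomly sample at least 50 charts per site", and the stated aim is "95% confidence intervals with widths no greater than +/− 10% for percentages of patients meeting quality measures (QMs) within each site".

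Table 2 (Evaluation) describes the outcome as "Quality of care (eg. appropriate prescribing of rifaximin, screening for frailty, time to post discharge follow up". In that row the data source is chart reviews, the method is interrupted time series, and phases 1 and 3 are marked. Table 3 includes the measure that recently discharged patients "should have a clinic visit with a health care provider within 4 weeks of discharge".

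Under Phase 3 – implementation, the phase opens with go-live "of the CCAB order set in the provincial CIS at each site", its "timing determined by timing of CIS implementation across the province (months 12–33"). Study setting explains that the new system is meant to "consolidate 1300 clinical information systems in use across the province", and that it should make practice more uniform and open records across hospital sites. The Discussion confirms that the study calendar follows the CIS rollout. Its limitations cover the lack of randomization, the fixed rollout, COVID-19 and attribution to single order-set components. A change in how care is recorded is not among them.

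**The concern.** An interrupted time series credits the intervention with whatever changes at the interruption, beyond the earlier trend. Here the instrument that reads the outcome is replaced by the same rollout that dates the interruption. Phase 1 charts are in the older systems and phase 3 charts are in the new CIS. If a larger or smaller share of the care given can be found in the new charts, the measured percentage moves at go-live although care has not changed.

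Time to post-discharge follow-up is exposed because the visit takes place after the audited admission, and finding it depends on what the chart can reach. Education and counselling are exposed because they count only if someone wrote them down. At stake is the answer to the effectiveness question on whether the order set raises quality of care, which is a secondary outcome.

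**Working it through.** **1. The plan's own figure.** The only figure given for this outcome is the ±10-point precision with 50 charts per site. The half-width is 1.96 × √(p(1−p)/50): 13.9 points at p = 50%, 12.7 at 30% and 13.6 at 60%. It is 10 or less only for p up to about 15% or from about 85%. So the stated figure does not reproduce over most of the range. That is a separate matter and lends no weight to the present point.

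**2. The passages side by side.**
- Source: chart reviews (Table 2, Quality Measures row); administrative and chart audits (quality of care section, without saying which measures come from which).
- Comparison: phase 1 with phase 3, by interrupted time series (Table 2).
- Start of phase 3: go-live of the order set inside the new CIS, timed by CIS implementation (Phase 3 – implementation).
- What else the CIS rollout changes: the record system and access to records across hospital sites (Study setting).
- Design features described that would separate recording from care: none. The article describes no site with the CIS but without the order set, and no planned lag between the two.

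**3. Size of an artefact when care is unchanged.** Let p be the share of patients who truly receive the care and s the share of delivered care that the chart shows. Recorded attainment is p × s, and the apparent change is p × (s after − s before). The range for p is 30% to 60%, the guideline-use range in Background. The values of s are assumptions, because the article gives no figure for chart completeness.

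| p | s 80%→90% | s 70%→90% | s 70%→95% | s 90%→80% |
|---|---|---|---|---|
| 30% | +3.0 | +6.0 | +7.5 | −3.0 |
| 50% | +5.0 | +10.0 | +12.5 | −5.0 |
| 60% | +6.0 | +12.0 | +15.0 | −6.0 |

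Entries are percentage points. For example, 0.60 × (0.95 − 0.70) = 0.15.

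**4. Could it reach significance?** Assume one sample of 8 × 50 = 400 charts before and 400 after. (The article does not say whether the 50 charts are per period or per quarter.) Take a two-sided 5% comparison of two proportions and ignore clustering.
- p = 50%, 80%→90% (40% v 45% recorded): probability 0.30.
- p = 50%, 70%→90% (35% v 45% recorded): probability 0.82.
- 70%→90% at p = 30% and at p = 60%: probability 0.51 and 0.93.

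This simple test is not the planned model, so the probabilities are only a guide.

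**5. Does staggering help?** Take eight sites, 48 months and illustrative go-live months 12, 15, 18, …, 33. The design matrix has 8 site intercepts, one time term, a CIS indicator and an order-set indicator, which makes 11 columns. If CIS and order set start together at each site, its rank is 10: the two indicators are identical and their effects cannot be separated. With a lag of 1 or 3 months the rank is 11, so separation is possible in principle.

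**The case against.** A reader might infer more: that charts are the only source, that better documentation will show up as better care, and that the quality conclusion is biased upward. The documents do not support that reading, for these reasons.

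- **Direction and size are not documented.** No completeness figure is given before or after go-live, and a new system may lower recording at first. The 30% to 60% in Background is itself reported guideline use, so applying a capture rate to it may discount under-recording twice. This stands. Only a possible artefact can be claimed.
- **Same-day start is inferred.** The text ties go-live to CIS timing, but Fig. 2 is not shown. A site where the CIS came first would allow partial separation. This stands as a condition.
- **Some measures are met by the record or order as defined.** Goals of care must be documented and a diet must be prescribed (Table 3). For these, a missing entry is a true failure and an order is a true success. This stands. The remaining point is interpretation: they show documentation or ordering, not care received.
- **Wider access is promised only across hospital sites.** Nothing says that primary-care visits become visible in the new record. This stands, and it leaves the direction for the 4-week visit open.
- **Administrative data are also mentioned, and an article may leave the source of each measure to a fuller document.** That detail is rightly not faulted. Table 2 nevertheless states chart review for this outcome and names time to follow-up in the same row, which is a stated choice.

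The structure survives: the source of the measure changes with the intervention, and the limitations do not say so.

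**Conclusion.** The point holds as a possible distortion of a secondary outcome. As described, a step in recording at go-live cannot be told apart from a step in care for measures that depend on what the chart shows. Trend adjustment removes earlier trends, not a step at the interruption, and staggering does not help where both changes start together at a site.

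Under assumed gains in capture of 10 to 25 points and true performance of 30% to 60%, the artefact is about +3 to +15 points. If capture first falls by 10 points, it is −3 to −6. These sizes rest on assumed capture rates and on a simultaneous start. Measures with an administrative source outside the chart are less exposed. Cumulative 90-day length of stay, the primary outcome, is not affected by this point.

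**What to change.** - In Table 2 and in the quality of care section, score the 4-week post-discharge visit (time to follow-up) from administrative outpatient data in both phases. Outpatient visit rate is already a secondary clinical outcome, and Table 2 lists administrative data among the sources for clinical outcomes. Confirm that this source covers both primary and specialty visits and was itself unchanged at go-live.
- Do the same for any other measure with an administrative source common to both phases. The article does not describe dispensing or procedure records, so their use depends on whether they exist in both phases.
- Base the conclusion on increased quality of care mainly on these measures.
- Report measures that rest only on chart documentation or on an order separately, labelled as such.
- Add the change of recording system to the limitations.

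The cost is wording, some linkage work, and fewer measures to carry the main quality-of-care claim.

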**Management of Cirrhosis complications**	
Ascites	*Patients undergoing large volume paracentesis (> 5 l removed) should receive intravenous albumin (6–8 g per liter removed)
Hepatic hydrothorax	*Patients with ascites and/or hepatic hydrothorax should be managed with both sodium restriction and diuretics (unless there is a contraindication for diuretics)
Spontaneous bacterial peritonitis	*Hospitalized patients with ascites, with an ascitic fluid polymorphonuclear count of ≥250 cells/mm^3^, should receive empiric antibiotics and albumin within 12 h of the test result. The first dose of albumin should be 1.5 g per kg body weight followed by a second infusion of 1.0 g/kg on day 3
Spontaneous bacterial pleuritis	*Hospitalized patients with a pleural fluid polymorphonuclear count of ≥500 cells/mm3 (or ≥ 250 cells/mm3 with positive culture), should receive empiric antibiotics within 12 h of the test result
Renal dysfunction	Patients with acute kidney injury should be given an intravenous albumin challenge of up to 100 g × 2 days.
Hepatorenal syndrome	Patients with cirrhosis and hepatorenal syndrome who have a MAP of < 65 mmHg should receive a combination of vasoconstrictors and albumin therapy
Variceal bleed	*Patients with cirrhosis who survive an episode of acute variceal hemorrhage should receive a combination of EVL (endoscopic variceal ligation) and β -blockers
Hepatic encephalopathy	*Patients who are discharged after an acute episode of hepatic encephalopathy should receive secondary prophylaxis with lactulose and/or rifaximin
Alcoholic hepatitis	Patients with ETOH hepatitis and a MELD score of > 20 should be considered for prednisone therapy provided there are no contraindications

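### The ±10-point per-site precision treats all 50 random charts as eligible, but ten of the fifteen measures in Table 3 can be scored only in charts with a trigger

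*Protocol article*

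**What the plan says.** The sample-size paragraph under 'Effectiveness outcome - quality of care measures' sets the rule: "We will randomly sample at least 50 charts per site". It then states the precision: "This will provide 95% confidence intervals with widths no greater than +/− 10% for percentages of patients meeting quality measures (QMs) within each site". The data-collection paragraph names administrative data together with "chart review data audits from randomly selected charts and will take place quarterly during the study", and adds "We will use inverse sampling weights to estimate the percent of patients attaining the QMs for the province". It mentions neither selection by complication nor a minimum number of eligible charts per measure.

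Table 3 gives a sample of fifteen measures, nine of them on cirrhosis complications. Each of the nine is restricted to patients with a named condition, finding or procedure. Two examples of the denominators are "Patients with cirrhosis and hepatorenal syndrome who have a MAP of < 65 mmHg" and "Hospitalized patients with a pleural fluid polymorphonuclear count of" a stated threshold. The alcohol measure, in the broader-needs block, is restricted to a positive screen. The other five (goals of care, diet, education, laboratory information, follow-up visit) apply to all admitted or discharged patients.

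The quality row of Table 2 lists chart review as the data source and interrupted time series across phases 1 and 3 as the analysis. Its examples are "appropriate prescribing of rifaximin, screening for frailty, time to post discharge follow up".

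**The concern.** The precision statement covers the quality measures in general and uses the number of charts as the denominator. For a conditional measure the denominator is the number of charts with the trigger, which under random sampling is 50 times the trigger frequency on average, with no guaranteed minimum.

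Quality of care is a listed secondary effectiveness outcome, evaluated in all three order-set domains, and the audits are meant to drive change at each site. The complication domain consists entirely of conditional measures in Table 3. If a site has only a handful of eligible charts, a movement in its percentage cannot be told from chance, and a site could be steered by noise.

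**Working it through.** **Inputs from the article.** At least 50 random charts per site; 95% intervals; a ±10-point target within each site; eight sites; 9 + 1 = 10 of 15 listed measures conditional.

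**Assumption.** The article gives no trigger frequency *q*. The only related figure is in the Background: more than 50% of cirrhosis admissions are attributable to alcohol, a proxy at best for a positive screen. A range of *q* is therefore used.

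**Step 1. The plan's own figure, with every chart eligible.** Half-width = 1.96 × √(p(1−p)/n). At p = 0.5 and n = 50 this is 1.96 × √(0.25/50) = 13.9 points (Wilson 13.4, exact 14.5). It falls to 10 points only when p is about 0.85 or above, or 0.15 or below. A worst-case ±10 points needs 1.96² × 0.25 / 0.10² ≈ 96.04, so 97 charts. The stated figure is therefore not reproduced at mid-range percentages even for measures that apply to everyone.

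**Step 2. Conditional measures, one draw of 50 charts at one site.** Expected eligible charts = 50q. P(none) = (1−q)^50. P(fewer than five) is the binomial probability of 0 to 4 in 50. Half-widths are exact (Clopper-Pearson) near 50% attainment.

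| Assumed q | Eligible of 50 | Exact half-width | P(none) | P(fewer than 5) |
|---|---|---|---|---|
| 2% | 1 | not usable | 36% | over 99% |
| 5% | 2.5 | not usable | 7.7% | 90% |
| 10% | 5 | about 40 points | 0.5% | 43% |
| 20% | 10 | about 31 points | below 0.1% | 2% |
| 30% | 15 | about 26 points | below 0.1% | below 0.1% |

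At q = 50% there are 25 eligible charts and the normal-approximation half-width is still about 20 points.

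**Step 3. Random charts needed for 97 eligible ones at a site.** 97/q gives 970 at q = 10%, 485 at 20% and 194 at 50%.

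**Step 4. Pooled over eight sites.** One draw gives 8 × 50 = 400 charts, so 400q eligible: 20, 40, 80 and 120 at q = 5%, 10%, 20% and 30%. The normal-approximation half-widths at p = 0.5 are about 22, 15, 11 and 9 points, before any loss from weighting or clustering.

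**Step 5. What the 50 refers to.** The article does not say whether 50 is per quarter, per period or in total. If it is the total over four years, that is 50/16 ≈ 3 charts per site-quarter. If it is per quarter, a site accumulates 16 × 50 = 800 charts, with 40 eligible at q = 5% and 80 at 10%. Each quarterly point still rests on 2.5 or 5 eligible charts.

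**The case against.** Several points on the other side stand.

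- **Frequencies are unknown.** A reader might infer that most audited charts contribute nothing to the ten measures. The article does not support that. The hydrothorax row takes in any patient with ascites, which is not shown to be rare, and the alcohol figure suggests that row may be well filled. A chart can also count for one measure and not another. Assuming independence, 1 − 0.95^10 = 40% of charts would score on at least one of the ten if each trigger had a frequency of 5%, and 1 − 0.90^10 = 65% at 10%.
- **Fifty is a minimum and audits repeat.** Eligible charts rise in proportion to charts drawn, so more random charts do help, though slowly for rare triggers (Step 3).
- **Charts are not the only source.** Some measures may be scored from administrative data and would not depend on the 50. Table 2 lists only chart review for quality, so the split is unclear.
- **Pooling is planned.** A reader might infer that the trial could not tell whether complication care improved. That goes too far: the weighted provincial estimate and the mixed models draw on all sites.
- **A finite-population correction could be meant.** With 2652/8/4 ≈ 83 patients per site-quarter, the Step 1 half-width falls from 13.9 to 8.8 points. The article states no such correction. The same factor (8.8/13.9 ≈ 0.63) would take the 40 points at five eligible charts only to about 25.
- **It is an article.** Sampling strata behind the weights are detail that the full protocol may hold, and Table 3 is expressly a sample, so ten of fifteen does not describe the full set.

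None of this rescues the statement made: a ±10-point interval within each site, from a chart count that ignores eligibility.

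**Conclusion.** The point holds in a limited form. The article claims a per-site precision that 50 random charts do not give for conditional measures, and ten of the fifteen listed are conditional. At assumed trigger frequencies of 10% to 30%, the half-width from one draw is about 40 to 26 points against the stated 10. At 5% or less there are too few eligible charts for a usable site-level interval. These sizes rest on the assumed frequencies, attainment near 50% and one draw of 50. They are milder for common triggers, for attainment near 0 or 100%, for pooled estimates, and if 50 charts are drawn each quarter and accumulated. This affects a secondary outcome and should be corrected. It does not touch the primary analysis of length of stay.

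**What to change.** 1. Restate the ±10-point figure by the expected number of eligible charts for each measure, with the assumed trigger frequencies shown. State whether 50 is per quarter, per period or in total.
2. Within the same number of charts, oversample admissions with the rarer complications, using administrative codes as a screen. Keep a random remainder for the measures that apply to all patients. Carry the selection probabilities into the inverse sampling weights already planned.
3. Report rare-trigger measures only as pooled provincial pre/post estimates, not by site or quarter.

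The cost is a pre-screen before each draw and somewhat wider intervals for the universal measures, because fewer charts are drawn purely at random and the weights become unequal. The screen will be imperfect: several triggers are laboratory or bedside values, and the article reports validation only for the codes that identify cirrhosis itself. Stratification alone does not restore site-level precision. Fifty charts over nine complications is 50/9 ≈ 5.6 each before any random remainder, overlap aside, which is why the pooled-only reporting rule is needed as well.
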